### Participant timeline

The schedule of trial enrollment, interventions, and assessments is presented in Fig. 2. Participant study visits will include a randomization visit, pregnancy study visits every 4 weeks until delivery, a delivery visit, and a postnatal visit scheduled after 42 days postpartum (discharge). Mothers who have a fetal loss or a newborn death will be followed up after 42 days to ascertain maternal mortality. Participant retention will be promoted at clinic visits and through phone calls and home visits.

**Fig. 2 Fig2:**
[figure not shown]
Schedule of enrollment, interventions, and assessments (SPIRIT figure)

### Pregnancy study visits

All pregnant women will have a research visit at the time of randomization and every 4 weeks during pregnancy until the time of delivery. Starting at 32 weeks gestation, all women will also receive weekly phone calls and, if possible, will be asked to call the study team around the time of labor. All women will receive an ultrasound for gestational dating around the time of the randomization visit or shortly thereafter. In India, the ultrasounds will be performed by trained and authorized radiologists/sonographers using the ultrasound machines available at each facility. For quality control, [name] of the St. John’s Medical College Hospital will review images for each sonographer at the study sites every 6 months. In Tanzania, trained nurses will conduct ultrasounds with General Electronic Vscan Access portable ultrasound machines. All ultrasound images for the Tanzania site will be electronically stored and a random 10% for the duration of the trial will be assessed for quality by [name] and [name] (sonographer) of the Beth Israel Deaconess Medical Center in Boston and feedback will be given to sonographers in Tanzania for quality improvement.

At all prenatal visits, study physicians will perform a full clinical examination, and treat all comorbidities in accordance with standard of care. Blood pressure will be assessed at randomization and at each pregnancy study visit. Electronic blood pressure monitors will be used in India (Omron HEM-7130, Kyoto, Japan) and Tanzania (Omron HEM-7131, Kyoto, Japan). Blood pressure assessment will be standardized by having all participants rest in a seated position for 5 min, placing the cuff on the left arm at the level of the heart and taking two blood pressure measurements (systolic and diastolic) at a 30-s interval. The electronic blood pressure machines will be calibrated once a month against a mercury sphygmomanometer; the electronic blood pressure machine will be discontinued from use in the study if the measured difference from the mercury sphygmomanometer is greater than 5 mmHg for systolic or diastolic blood pressure. Participants will be asked by study staff to provide urine at the randomization and each pregnancy follow-up visits, and the presence of protein will be assessed with a dipstick. Research staff will collect maternal height with calibrated stadiometers to the nearest 0.1 cm at the randomization visit. At randomization and all follow-up visits, maternal weight will be taken on digital weighing scales to the nearest 0.01 kg and the mid-upper arm circumference (MUAC) will be taken with a measuring tape to the nearest 0.1 cm. The weighing scales will be calibrated each day using certified 5, 10, and 20 kg weights. Pregnant women will have a finger-prick blood sample collected at randomization and at 32 weeks gestation for assessment of hemoglobin concentration (HemoCue Hb 301 in India and HemoCue Hb 201 in Tanzania, HemoCue AB, Ängelholm, Sweden). Hemocue machines will be calibrated each day using the tri-level control solutions provided by the manufacturer. Maternal dietary intake will be assessed with an open-ended 24-h diet recall conducted once during each trimester of pregnancy. Maternal depression will be assessed with the Patient Health Questionnaire (PHQ)-9 at randomization and at the 6 week postpartum visit [17]. We will also seek consent to collect 8 ml of venous blood specimen at randomization and 32 weeks gestation from participants enrolled at each site starting in January 2021 to understand the pathophysiology of hypertensive diseases of pregnancy and preterm birth using a nested case-cohort study design. Blood specimen will be collected in two vacutainers (4 ml each) with the anticoagulant ethylenediamine tetraacetic acid (EDTA) and temporarily stored in a cool box with icepacks until they are transported to a central laboratory at each site for processing within 4 h of collection in order to maintain the cold chain. At the laboratory, trained study technicians will centrifuge the blood specimen tubes to separate the plasma, which will then be aliquoted into multiple, prelabelled cryovials for long-term storage at − 80 °C freezers. Serum samples will be tested for biomarkers of calcium metabolism, pro- and anti-angiogenic profile, and other potential biomarkers related to preeclampsia and preterm birth. The selection of biomarkers and laboratory methods will be finalized in collaboration with the trials’ Technical Advisory Group in mid-2022 and will account for emerging evidence on the pathophysiology of preeclampsia and preterm birth. Study participants who consent for blood collection will also be asked for consent for long-term storage of serum samples and dried blood spots and their use in ancillary studies.

### Labor and delivery study visit

Study staff will be available throughout the day and night to attend labor and delivery of participants. Participants who deliver outside of the study area will be reached by phone by the research staff to obtain relevant information from the mother and/or facility records. Clinic records and interviews with the clinic staff and participants will be used to ascertain the duration of each stage of labor, labor complications, and Apgar scores at 1 and 5 min for the newborns. Maternal blood pressure and proteinuria will be assessed by clinic or study staff or collected from clinic records. Infant length and weight will also be taken by study staff or recorded from facility records. Infant weight will be measured to the nearest gram using a digital scale and length with the use of a rigid length board with an adjustable foot piece to 1-mm precision. Verbal autopsies will be conducted to ascertain causes of maternal deaths [18].

### Postpartum study visit

Women or women/infant pairs will have a study visit at 6 weeks postpartum (42 days) and will be discharged from the trial after completion of this visit. At the postpartum visit, research staff will assess maternal and infant morbidity and hospitalization history. Nurses will also collect weight and, blood pressure from mothers. Study nurses will assess infant feeding, infant weight with a digital infant balance scale to the nearest gram and length to 1-mm precision with a rigid length board with an adjustable foot piece. Study nurses will measure infant head circumference and mid-upper arm circumference (MUAC) with flexible measuring tape. All infant anthropometric measurements will be recorded in duplicate. Verbal autopsies will be conducted to ascertain causes of infant deaths [18].

### Data management

All data will be entered into independent electronic data capture systems in Tanzania and India, and the program will have in-built skip patterns and range check validations for each variable. All identifiable electronic data will remain in India and Tanzania and will be stored on secure local servers that are only accessible by the respective study data teams and Investigators.

## Outcomes

A summary table of the primary outcomes and definitions is presented in Table 2. The primary outcomes for the trials are (i) preeclampsia and (ii) preterm birth. Preeclampsia will be defined by the presence of both gestational hypertension and gestational proteinuria among participants without chronic hypertension, gestational proteinuria among participants with chronic hypertension (superimposed preeclampsia), clinical diagnosis of preeclampsia, or development of severe features with or without proteinuria [1, 21]. A primary outcomes committee composed of the trial investigators and led by a maternal-fetal medicine physician ([name]) will review all potential preeclampsia events blinded to randomized treatment group using established criteria. The preeclampsia event will be confirmed if the majority of the committee members are in agreement with a preeclampsia diagnosis.

**Table 2 Tab2:** Summary of primary and secondary outcome definitions and analytic populations

Primary outcomes	Definition
Preeclampsia	Gestational hypertension and gestational proteinuria among participants without chronic hypertension; or, gestational proteinuria among participants with chronic hypertension (superimposed preeclampsia); or, clinical diagnosis of preeclampsia by managing clinical team; or, development of severe features of preeclampsia with or without proteinuria
Preterm birth	Live birth < 37 weeks completed weeks gestation
**Secondary outcomes**	**Definition**
Gestational hypertension	A systolic blood pressure ≥ 140 mm Hg on two occasions at least 1 h apart; or, diastolic blood pressure ≥ 90 mm Hg on two occasions at least 1 h apart; or, severe gestational hypertension in pregnancy among participants without chronic hypertension, defined in the antenatal period as systolic blood pressure ≥ 160 mmHg or a diastolic blood pressure ≥ 110 mmHg on two occasions at least 1 min apart after 20 weeks gestation and defined at the time of labor/delivery as requiring only one systolic blood pressure ≥ 160 mmHg or a diastolic blood pressure ≥ 110 mmHg. Note: Chronic hypertension defined by a clinical diagnosis of chronic hypertension (with or without need for medication) or systolic blood pressure ≥ 140 mm Hg on two occasions at least 1 h apart or diastolic blood pressure ≥ 90 mm Hg on two occasions at least 1 h apart before 20 weeks’ gestation.
Severe features of preeclampsia	The following will be defined as severe features of preeclampsia: • Severe gestational hypertension (with or without proteinuria), or • Eclampsia, or • Evidence of end organ dysfunction by laboratory criteria, or • Clinical diagnosis of HELLP syndrome (hemolysis, elevated liver function, low platelets), or • Development of pulmonary edema, or • New onset CNS or visual symptoms
Pregnancy-related death within 42 days of termination of pregnancy	Death of a woman while pregnant or within 42 days of termination of pregnancy, irrespective of the cause of death
Third trimester severe anemia (targeted safety outcome)	Hemoglobin concentration < 7.0 g/dL [19]
Fetal death	A product of human conception, irrespective of the duration of the pregnancy, which, after expulsion or extraction, does *not* breath or show any other evidence of life such as beating of the heart, pulsation of the umbilical cord, or definite movement of voluntary muscles, whether or not the umbilical cord has been cut or the placenta is attached [20]
Stillbirth	Fetal death ≥ 28 weeks gestation
Low birthweight	Live birth weighing < 2500 g
Small-for-gestational age birth	Live birth with size-for-gestational age < 10th percentile on the INTERGROWTH-21st standard
Infant death < 42 days	Death of a live birth during the first 42 completed days of life (6 weeks postpartum)

The co-primary outcome of preterm birth will be defined as a live birth born < 37 completed weeks gestation. We will use the best obstetric estimate (BOE) approach for gestational age dating which combines information from date of last menstrual period (LMP) and fetal biometric measures from ultrasound assessment. Ultrasound-based gestational age will be assessed using INTERGROWTH-21st equations for gestational age assessment for crown-rump length, head circumference, and femur length, or the Hadlock equations for biparietal diameter and femur length, using a hierarchical approach (Additional file 3) [22, 23]. First and second trimester fetal biometric measures will be used when possible. Ultrasound-based gestational age will be used if the estimated date of delivery (EDD) based on fetal biometric measures differs from LMP-based EDD according to guidelines established by the Society for Maternal-Fetal Medicine and the American College of Obstetrics and Gynecology (Additional file 3) [24]. For any participant for whom ultrasound scans could not be conducted, are not available, or are deemed to be invalid, LMP-based GA will be used.

The secondary trials outcomes and definitions are presented in Table 2. Third trimester severe anemia (hemoglobin concentration < 7.0 g/dL) was identified as a targeted safety outcome that will be reported as a secondary outcome in the main trial report. All women will have hemoglobin concentrations assessed at 32 weeks gestation. Calcium supplements can reduce absorption of iron and therefore may increase the risk of anemia [10].

## Statistical methods

The India and Tanzania trials will be analyzed independently; however, the outcome definitions and statistical methods will be the same for both trials. An intent-to-treat (ITT) analysis will be the primary approach for all analyses and one-sided tests for non-inferiority with a type I error rate of 0.05 will be used. The ITT analysis for preeclampsia will include all randomized women and the preterm birth ITT analysis will include all livebirths. A complete case analysis will be used in the primary analyses.

For preeclampsia, we will use a log-binomial model with a fixed effect for study clinic to account for the stratified randomization scheme to produce relative risk estimates for the preeclampsia outcome for the low-dose as compared to the standard high-dose calcium supplementation group. The upper bound of the 90% confidence interval of the relative risk for preeclampsia will be compared with the prespecified noninferiority margin to assess non-inferiority. The primary analysis for preeclampsia will be among all randomized participants. We will conduct a sensitivity analysis for preeclampsia excluding pregnancy losses and participants who withdraw before 20 weeks gestation. In addition, we will also construct Kaplan–Meier curves with gestational age as the time metric to visualize the incidence of preeclampsia between randomized groups. We will present relative risks and 90% confidence intervals but will not formally test non-inferiority for any preeclampsia sensitivity analyses.

For preterm birth, a generalized estimating equation (GEE) analysis with the log link, a fixed effect for study clinic and a compound symmetry working correlation matrix to account for correlations due to multiple gestation will be used to construct relative risks for preterm birth among live births between randomized groups. The 90% confidence intervals of the relative risk will be compared with the prespecified non-inferiority margin to assess non-inferiority. We will conduct a sensitivity analysis for preterm birth among singleton pregnancies and will present relative risks and 90% confidence intervals but will not formally test non-inferiority.

We will also conduct a per-protocol analysis for preeclampsia and preterm birth. The per-protocol analysis for preeclampsia will include all participants who had > 75% adherence to the supplementation regimen based on pill count, had a pregnancy ≥ 20 weeks gestation, and had a delivery outcome assessed (excluding withdrawal and loss-to-follow-up in pregnancy). The per-protocol analysis for preterm birth will include all participants who had > 75% adherence to the supplementation regimen and a live birth. We will present relative risks and 90% confidence intervals for the per-protocol analyses but will not formally test non-inferiority.

We will use similar methods for analysis of secondary binomial maternal and infant outcomes (Table 2). We will present relative risks and 95% confidence intervals for secondary outcomes but will not formally test non-inferiority between randomized groups.

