### Assignment of interventions: allocation and blinding

In both trials, pregnant women who consent for enrollment will be individually randomized in a 1:1 ratio to either the (i) low-dose 500 mg calcium supplementation group or (ii) the standard high-dose 1500 mg calcium supplementation. The allocation sequence was generated by a statistician in Boston for each trial separately (India and Tanzania) using a computer-generated randomization list of 11,000 individuals with block randomization, stratified by study clinic. Two non-study staff hold the randomization list codes until completion of primary analyses or until requested by the Data and Safety Monitoring Board (DSMB). An independent study pharmacist in each country will privately prepare the 500 mg and 1500 mg regimen boxes with participant IDs based on the randomization list. At the randomization visit, research staff will assign pregnant women who are eligible and consent for trial randomization to the next available participant ID which corresponds to a set of pre-labeled regimen boxes. The trial statistician and data analysts will also be blinded to treatment allocation for the primary statistical analysis. As a result, the trial is quadruple blind with all trial participants, research staff, and care providers, Investigators, outcome assessors, and trials statistician and data analysts being unable to determine the allocated trial arm for any trial participant or identify trial participants who are on the same trial regimen. Further, the randomization procedures ensure complete allocation concealment. The DSMB, Institutional Review Boards (IRBs), attending physicians, and Principal Investigators may request to unblind a participant(s) allocated trial group during the trial for safety reasons.

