### Sample size

The sample size for each trial will be 11,000 participants. Statistical power for the primary outcomes of preeclampsia and preterm birth was calculated using formulas for binomial outcomes in non-inferiority trials [15]. Power calculations assumed 1:1 randomization, a one-sided test with a type I error rate (α) of 0.05, and a 10% loss-to-follow-up rate (including pregnancy loss for preterm outcome). The non-inferiority margin for each primary outcome was selected by the trials’ Technical Advisory Group. The non-inferiority margin for preeclampsia was set at a relative risk of 1.54 for low-dose calcium as compared to the standard high-dose calcium based on the lower bound of the 90% confidence interval for the effect of standard high-dose calcium versus placebo on preeclampsia [9, 16]. The non-inferiority margin for preterm birth was set at a relative risk of 1.16 for low-dose calcium as compared to the standard high-dose calcium regimen to maintain 50% of the effect based on the point estimate of the relative risk for the effect of standard high-dose calcium versus placebo on preterm birth (relative risk = 1.32) [9, 16]. The exact cumulative incidence of preeclampsia and proportion of preterm birth in the standard high-dose calcium arm was not known for the India and Tanzania sites, and therefore, power calculations were presented for a plausible range of cumulative incidence of preeclampsia of 1.5 to 5% and a proportion of preterm birth of 10.0 to 13.5%. Table 1 presents statistical power in each trial for the plausible range of preeclampsia and preterm birth in the standard high-dose calcium group. For preeclampsia, each trial will have ~ 95% power if the cumulative incidence of preeclampsia is as low as 1.5% in the standard high-dose group and > 99.9% if the incidence is high at 5%. For preterm birth, each trial will have 84.3% power if the cumulative incidence is as low as 10% in the standard high-dose group and > 99.9% if the incidence is as high as 13.5%.

**Table 1 Tab1:** Statistical power for primary outcomes of preeclampsia and preterm birth for each trial site based on a one-sided test with a type I error rate of 0.05 (India = 11,000 participants; Tanzania 11,000 participants)

		Cumulative incidence of preeclampsia in standard high-dose calcium group (1500 mg/day)		
		1.5%	3%	5%
**Statistical power for preeclampsia**	Noninferiority margin—relative risk of 1.54	**95.3%**	**99.9%**	**> 99.9%**

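### The primary models are valid but adjust for clinic only; standardising for blood pressure and other values known at randomization would buy a small, low-cost gain in precision

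*Protocol article*

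**What the plan says.** All places are in the protocol article.

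- **Statistical methods, preeclampsia:** "we will use a log-binomial model with a fixed effect for study clinic to account for the stratified randomization scheme". The upper 90% confidence limit of the relative risk is compared with the margin.
- **Statistical methods, preterm birth:** "a generalized estimating equation (GEE) analysis with the log link, a fixed effect for study clinic and a compound symmetry working correlation matrix".
- **Assignment of interventions:** allocation uses "a computer-generated randomization list of 11,000 individuals with block randomization, stratified by study clinic". Clinic is the only stratification factor named.
- **Pregnancy study visits:** "Blood pressure will be assessed at randomization and at each pregnancy study visit". Height and weight are also measured when a woman is randomized, height by stadiometer and weight on digital scales.
- **Sample size:** "The sample size for each trial will be 11,000 participants", and "Power calculations assumed 1:1 randomization, a one-sided test with a type I error rate (α) of 0.05, and a 10% loss-to-follow-up rate". No gain from covariates is assumed.

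Sensitivity and per-protocol analyses are reported without a formal non-inferiority test, so the clinic-only models carry the decision.

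**The concern.** Non-inferiority turns on one upper confidence limit per outcome, so any reduction in the variance of the log relative risk acts directly on the decision. Blood pressure at randomization is a plausible predictor of preeclampsia. Chronic hypertension is not an exclusion criterion. Under the Outcomes section, a woman with chronic hypertension can meet the endpoint through gestational proteinuria alone, whereas the corresponding route for other women needs hypertension as well. Blood pressure early in pregnancy therefore bears on which branch of the definition applies.

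A supportive adjusted analysis in an analysis plan not shown here would not achieve the same thing, because only the primary model is tested. What is at stake is a little power, not validity.

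**Working it through.** **Inputs from the protocol article.** 11,000 women per trial, 1:1, 10% loss, so n = 11,000 × 0.9 / 2 = 4,950 per arm. One-sided alpha 0.05 (z = 1.645). Margins M: 1.54 for preeclampsia, 1.16 for preterm birth. High-dose risks p: 1.5% to 5% and 10% to 13.5%. True relative risk 1.

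**Step 1: reproduce Table 1.** Table 1 is matched by power = Φ(p(M − 1) / √(2p(1 − p)/n) − 1.645).

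- Preeclampsia, 1.5%: 0.0081 / 0.002443 = 3.315; power 95.3% (stated 95.3%).
- Preterm birth, 10%: 0.0160 / 0.006030 = 2.653; power 84.3% (stated 84.3%).
- The other entries also reproduce: 99.9% and > 99.9%; 91.4% and 93.3%.

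**Step 2: move to the scale of the planned models.** These estimate a relative risk, so the relevant quantity is Φ(ln M / SE − 1.645) with SE = √(2(1 − p)/(np)).

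- Preeclampsia, 1.5%: 0.4318 / 0.1629 = 2.651; power 84.3%.
- Preeclampsia, 3%: 0.4318 / 0.1143 = 3.778; power 98.4%.
- Preterm birth, 10%: 0.1484 / 0.0603 = 2.461; power 79.3%.

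These are the starting values for the comparison below. Their difference from Table 1 is a separate matter.

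**Step 3: gain from adjustment.** The documents give no strength of association, so I assume one baseline score with a stated odds ratio (OR) per SD in a logistic model. The share of outcome variance it explains is R² = var(risk) / (p(1 − p)). Adjustment multiplies the variance of the log relative risk by about 1 − R².

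| Outcome, p | OR per SD | R² | 90% CI width cut | Power, from → to |
|---|---|---|---|---|
| Preeclampsia 1.5% | 1.3 | 0.1% | 0.05% | 84.3% → 84.3% |
| Preeclampsia 1.5% | 2.0 | 0.9% | 0.4% | 84.3% → 84.6% |
| Preeclampsia 1.5% | 3.0 | 2.8% | 1.4% | 84.3% → 85.2% |
| Preeclampsia 3% | 3.0 | 4.9% | 2.5% | 98.4% → 98.7% |
| Preterm 10% | 1.3 | 0.6% | 0.3% | 79.3% → 79.5% |
| Preterm 10% | 1.5 | 1.5% | 0.8% | 79.3% → 79.8% |
| Preterm 10% | 2.0 | 4.5% | 2.3% | 79.3% → 80.9% |

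For scale, a 2% variance cut at an observed relative risk of 1 moves the upper 90% limit from 1.307 to 1.304 (preeclampsia, 1.5%) and from 1.104 to 1.103 (preterm birth, 10%).

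**Step 4: simulation check.** 2,000 trials of 9,900 women per row, log-link models with robust standard errors, without and with the score.

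| Outcome, p | OR per SD | SD of log RR | Power |
|---|---|---|---|
| Preeclampsia 1.5% | 2.0 | 0.1627 → 0.1621 | 83.4% → 83.5% |
| Preeclampsia 1.5% | 3.0 | 0.1637 → 0.1609 | 84.6% → 85.3% |
| Preterm 10% | 1.3 | 0.0585 → 0.0582 | 81.2% → 80.9% |
| Preterm 10% | 1.5 | 0.0601 → 0.0596 | 78.9% → 79.7% |
| Preterm 10% | 2.0 | 0.0623 → 0.0607 | 78.8% → 79.8% |

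The Monte Carlo standard error of one power figure is about √(0.8 × 0.2 / 2,000) = 0.9 points, so the small fall in the third row is noise. The simulation confirms the order of the gain, not its decimals. It adjusted inside a log-link model and did not run the standardised estimator itself.

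**The case against.** The strongest reply is that nothing here is wrong. Clinic is the stratification factor, the models adjust for it for that reason, and leaving out other covariates does not bias a relative risk in a randomized trial. All of that stands. The gain is also small, because baseline values explain little of the variance of an outcome this uncommon. For preeclampsia at 3% or 5%, Table 1 already gives 99.9% or more, so there is nothing to rescue.

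Two technical objections would count against simply adding terms to the planned models. Continuous covariates can make a log-binomial fit fail to converge, and a complete-case rule would drop women with a missing baseline value from an analysis meant to include everyone randomized. Neither applies to a logistic working model with standardisation and mean-imputed baseline values.

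The choice of covariates does need care, and this part of the objection stands.

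- **Chronic hypertension:** the definition can rest on readings at least 1 h apart, while study visits take two readings 30 s apart. The article does not say that a prior diagnosis is recorded at randomization.
- **Ultrasound dating:** the scan may follow randomization, so gestational age that relies on it is not strictly a baseline value.

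Both are therefore left out of the proposal.

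A reader might infer that the plan gives precision away for nothing, or that adjustment is worth several hundred women. The documents support neither. They never state that these measures predict the outcomes, the change is cheap but not free, and the larger savings in equivalent sample size come mainly from preeclampsia scenarios where power is already near 100%.

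**Conclusion.** The point holds as an optional improvement. Both decision-making models use arm and clinic only, although blood pressure, weight and height are available at randomization. Over the assumed prognostic range (OR per SD 1.3 to 3.0 for preeclampsia, 1.3 to 2.0 for preterm birth), adjustment adds about 0 to 1 point of power for preeclampsia at 1.5% and about 0 to 2 points for preterm birth at 10%. It has no decision value at higher preeclampsia incidence.

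These figures rest on a true relative risk of 1, 4,950 women per arm, the relative-risk scale, and a prognostic strength that the documents do not supply. The omission causes no bias and does not invalidate the planned test.

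**What to change.** Before unblinding, prespecify as the primary estimate a covariate-standardised marginal relative risk:

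1. Fit a logistic working model with arm, clinic, mean arterial pressure and BMI at randomization, maternal age, and LMP-based gestational age at randomization.
2. Mean-impute rare missing baseline values, so that no woman is lost on that account.
3. Average the predicted risks with everyone set to low dose and then to high dose, and take the ratio.
4. Use a robust or bootstrap 90% confidence interval, with variance clustered on the mother for preterm birth.
5. Compare the upper limit with the same margins, 1.54 and 1.16, and keep the clinic-only models as sensitivity analyses.

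No new data are needed. The cost is a little more specification and analysis work. In addition, the Oversight and monitoring section requires protocol modifications to be reported to the review boards, the Technical Advisory Group and the DSMB before they are implemented.

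### Kaplan–Meier curves over gestational age, with women censored when pregnancy ends, would plot a preeclampsia incidence above the crude risk, mainly from 39–40 weeks; Aalen–Johansen curves would not

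*Protocol article*

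**What the plan says.** The protocol article, under Statistical methods, plans Kaplan–Meier "curves with gestational age as the time metric to visualize the incidence of preeclampsia between randomized groups". It gives no censoring rule for these curves and does not mention competing events.

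The non-inferiority decision rests on something else: "we will use a log-binomial model with a fixed effect for study clinic to account for the stratified randomization scheme". The population is stated as well: "The primary analysis for preeclampsia will be among all randomized participants". The section then adds: "We will present relative risks and 90% confidence intervals but will not formally test non-inferiority for any preeclampsia sensitivity analyses".

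Under Pregnancy study visits, women are seen at randomization and "every 4 weeks during pregnancy until the time of delivery". Time on the gestational-age axis therefore ends with the pregnancy.

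**The concern.** The sentence pairs a named estimator with a named quantity, and the two do not match if the estimator is applied in the usual way. A woman who has delivered or lost the pregnancy accrues no further gestational age, so a standard Kaplan–Meier routine censors her at that point. It then treats her as if she would have gone on at the preeclampsia risk of the women still pregnant. This is how nearly every woman without the event leaves the curve, so it is not incidental dropout.

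What is at stake is how the figure is read. A reader would take the height of the curve at 40–42 weeks as the share of women who developed preeclampsia. It would be higher than the risks in the same report's primary analysis, with nothing in the planned description to explain the gap.

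**Working it through.** **1. The plan's own figure.** The article gives no number for the curves. The nearest is the Table 1 power for preeclampsia, which shows what incidence means elsewhere in the plan. Inputs from Sample size: "The sample size for each trial will be 11,000 participants"; "Power calculations assumed 1:1 randomization, a one-sided test with a type I error rate (α) of 0.05, and a 10% loss-to-follow-up rate"; "The non-inferiority margin for preeclampsia was set at a relative risk of 1.54". Per arm, n = 11,000/2 × 0.9 = 4,950. With a high-dose risk p = 0.015 and a true relative risk of 1:

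Power = Φ[(1.54 − 1) × 0.015 / √(2 × 0.015 × 0.985 / 4,950) − 1.645] = Φ(0.0081/0.002443 − 1.645) = Φ(1.67) = 95.3%.

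This matches Table 1. The planning incidence is thus a plain binomial proportion of women, as is the risk in the log-binomial model.

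**2. The two quantities.** Let h_j be the preeclampsia hazard in week j among women still pregnant and event-free, and S_j the proportion still pregnant and event-free after week j.

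- 1−KM, censoring at end of pregnancy: K(t) = 1 − Π(1 − h_j).
- Cumulative incidence, with end of pregnancy competing: F(t) = Σ h_j S_(j−1).

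K(t) can be written as the same sum with S_(j−1) replaced by Π(1 − h_i) over i < j. That product ignores deliveries and so is never below S_(j−1). Hence K(t) ≥ F(t) always, and the gap opens as deliveries accumulate. The direction needs no assumption beyond censoring at the end of pregnancy.

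**3. Inputs for the size.** From the article (Sample size and Table 1): crude risk 1.5%, 3% or 5%; preterm birth 10.0–13.5%. Assumed, because the article does not give them: the distribution of delivery weeks within those preterm rates, and how the weekly hazard changes with gestation.

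**4. Results** for a crude risk of 3% and preterm birth of 13.5% (F, K and K/F by week, for three weekly hazard growth rates):

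| Week | 0% growth | 10% growth | 20% growth |
|---|---|---|---|
| 37 | 2.73%, 2.80%, 1.03 | 2.39%, 2.49%, 1.04 | 1.98%, 2.10%, 1.06 |
| 39 | 2.94%, 3.10%, 1.06 | 2.84%, 3.14%, 1.11 | 2.69%, 3.14%, 1.17 |
| 40 | 2.98%, 3.25%, 1.09 | 2.96%, 3.52%, 1.19 | 2.91%, 3.84%, 1.32 |
| 41 | 3.00%, 3.41%, 1.14 | 2.99%, 3.93%, 1.31 | 2.99%, 4.68%, 1.57 |
| 42 | 3.00%, 3.56%, 1.19 | 3.00%, 4.39%, 1.46 | 3.00%, 5.70%, 1.90 |

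Over growth of 0–20% and preterm birth of 10–13.5%, 1−KM at 42 weeks is 1.76–2.87% for a crude 1.5%, 3.52–5.70% for 3%, and 5.86–9.43% for 5%.

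**5. Wider hazard range.** With weekly log-hazard growth from 0 to 0.30 (0.30 multiplies the hazard by e^0.30 = 1.35 each week), a 3% crude risk and preterm birth within 10–13.5%, the ratio is about 1.07–1.37 at 40 weeks, 1.11–1.69 at 41 and 1.15–2.2 at 42. At 37 weeks it is at most 1.06. A recalculation in continuous time with several delivery curves gave the same ranges to within about 0.03.

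**6. What would remove the gap.** If delivered event-free women stay in the risk set to the end of the axis, 1−KM equals the crude incidence. In one simulated scenario at 42.5 weeks this gave 2.31% against a true 2.31%, where censoring gave 3.51%.

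**7. Does a shift in delivery timing separate the curves?** Take deliveries with 6% spread over 28–37 weeks and the rest normal with mean 39.2 and SD 1.7 weeks. Hold the preeclampsia hazard fixed and move mean delivery 0.5 weeks earlier. At 41 weeks, 1−KM stays put within simulation error (4.0% and 4.0% at log-hazard growth 0.15; 4.8% and 4.7% at 0.30). The cumulative incidence does move (2.9% to 2.7%; 2.8% to 2.5%). This delivery curve implies 0.06 + 0.94 × Φ(−1.29) ≈ 15% preterm, above the article's range, so it is used only for this comparison. About 0.94 × 0.050 = 4.7% of its women are still pregnant at 42 weeks.

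**The case against.** The strongest reply is that the article states no censoring rule. The treatment of delivery in a descriptive plot could be settled in an analysis plan that is not shown, and one possible rule (step 6) removes the gap. This stands as a condition on the point. It does not dispose of it: the article has already named the estimator, the axis and the quantity, and an analyst following that sentence with default software would censor at the end of pregnancy.

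It can also be said that 1−KM and the crude risk are different estimands, so a difference between them is not a contradiction. That is fair. But the sentence presents the curve as showing incidence, which under censoring is the quantity it does not estimate.

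The large ratios depend on steep hazards and on weeks when few women remain pregnant. That also stands: with a flat hazard the ratio at 42 weeks is only about 1.15–1.19.

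A reader might infer more: because delivery timing is tied to the other co-primary outcome, preterm birth, a timing difference between arms would appear in the Kaplan–Meier curves as a spurious difference in preeclampsia. The material does not support this. With equal hazards, earlier delivery in one arm leaves 1−KM unchanged and moves the Aalen–Johansen curve instead (step 7). With similar timing in both arms, both curves inflate alike and their ratio is roughly kept: about 1.54 on both scales at 40 weeks in simulation. Nor does the article rank this plot as the main incidence figure; it is an additional display.

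**Conclusion.** The point holds as a minor one about a descriptive figure. Provided women are censored when pregnancy ends, 1−KM will exceed the crude cumulative risk. The direction is certain; the size is not. Before 37 weeks the excess is negligible (ratio at most about 1.06). With preterm birth of 10–13.5% and weekly log-hazard growth of 0 to 0.30, the ratio is about 1.1–1.4 at 40 weeks, 1.1–1.7 at 41 and 1.15–2.2 at 42. The hazard shape and the delivery-week distribution are assumptions, and the last figure concerns a small remaining group.

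The log-binomial relative risk, the comparison with the 1.54 margin, the power and the sample size are all untouched. No bias between arms is shown.

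**What to change.** Replace the Kaplan–Meier curves with Aalen–Johansen cumulative incidence curves by arm on the gestational-age axis. Treat end of pregnancy (delivery or loss) without preeclampsia as the competing event, and censor only withdrawal or loss to follow-up. The end of each curve then agrees, apart from losses, with the reported risks.

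The cost is one sentence and a standard routine, with no new data and no change to any test. There is one small downside: the new curve also reflects delivery timing, so it should be labelled as cumulative incidence and not read as a comparison of hazards.
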